### Study data

GPs in both the intervention and control groups have been provided with a menu button situated on the navigation bar of their practice management software () indicating the link to register patients for the study. GPs will click the button when they encounter a patient they believe to be suffering from a TIA or stroke. In the control group, the button click will prompt patient clinical details to be registered and stored centrally by BPAC and the GP will be advised to continue with routine care. In the intervention group, clicking the button will open up the TIA/stroke EDS module and the GP will then use the software. For each patient in the intervention group, information about diagnosis, triage advice, and management plan given to the GP by the EDS tool will be recorded and stored centrally at BPAC, in addition to patient clinical details.

Throughout the trial and at the end of the 12-month intervention period, records of all patients entered into the BPAC database via the procedure described above will be reviewed for outcome measures three or more months after being registered. GP records will be scrutinized and all data collected will be verified and supplemented by hospital and coroners’ records when applicable. Data collection will be accomplished by a study clinician via use of an electronic Microsoft Access tick box form to facilitate efficient data analysis.

Specific data collected about patients include: final diagnosis including anatomic localization (confirmed by specialist)—TIA, ischaemic stroke, hemorrhagic stroke, or other and anterior versus posterior localization; ABCD2 score if available; initial GP triage destination (community, hospital, or TIA clinic); past medical history of atrial fibrillation, current warfarin use, more than one TIA/stroke event over past seven days (all high risk indicators); medical treatment with antiplatelet(s), statin, and/or antihypertensive accomplished in <24 hours, 24 hours to 7 days, or >7 days; documentation of counseling/education (smoking, diet/exercise, driving, thrombolysis) and by whom it was provided (GP/practice nurse, hospital physician, hospital nurse); investigations and time frame (< 24 hours, 24 hours to 7 days, > 7 days) for ECG, CT head, MRI, echocardiogram, Holter monitor, and carotid ultrasound if obtained; hospital specialist review ‘yes/no’ in < 24 hours, 24 hours, to 7 days, > 7 hours; hospitalizations related to index event ‘yes/no,’ if yes number of days in hospital and discharge location; and TIA, stroke, MI, major bleeding or death within three months of index event, any significant adverse events attributable to medications prescribed after index event, diagnostic delays, and/or misdiagnosis (‘significant event’ is defined as an event that prompted a GP visit/phone call, hospitalization or death). All identifiable data will be expunged from the final dataset to be analyzed for the study, leaving patients identified only by a unique study code.

In addition, at the end of the study, GPs will be surveyed regarding satisfaction with the tool as regards usability, efficiency, and any patient concerns of which they have been made aware. Specialists providing care through a TIA clinic will be surveyed regarding satisfaction with referral quality and any concerns or observations they have made comparing management with versus without TIA/stroke EDS.

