To date, we have conducted four studies to assess the TIA/stroke decision support tool. A pre-launch community-based pilot indicated a high degree of GP satisfaction, excellent guideline adherence when the tool’s management advice was followed closely, and no adverse patient outcomes [22]. A second study comparing stroke experts, GPs, and decision support management in seven sample cases found that management was guideline adherent 33% among GPs without EDS, 92% among specialists, and 100% when the decision support tool was used [23]. Data from a before-and-after study in the MidCentral DHB showed that best medical therapy was in place within 24 hours in 31% of patients before introduction of the EDS system and 52% after its introduction [24]. Finally, a recent unpublished audit of all patients managed using the EDS for the 18 months following its launch has not found any significant adverse events associated with its use. Although reassuring and promising these small non-experimental studies support the need for a well-designed randomized controlled trial to assess this novel treatment approach.

The aim of the FASTEST trial is to formally test the efficacy and safety of New Zealand’s TIA/stroke decision support tool in comparison with usual care. This study has received funding from the Health Research Council of New Zealand (grant 11/268), ethics approval from the Ministry of Health Multi-region Ethics Committee (URA/11/08/048) and has been under way since November 2011.

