**Figure 1 F1:**
[figure not shown]
TIA/stroke EDS Data Entry Form with sample case.

Completing the page of background and clinical presentation data takes approximately two to five minutes depending on the GP’s familiarity with the tool. Based on this information, the software confirms or rejects TIA/stroke as the likely diagnosis. If TIA or stroke is confirmed, a triage recommendation is generated based on the validated ABCD2 risk score [25] supplemented by several other variables taken from the New Zealand TIA guidelines [13] (Figure 2). If patients are triaged into the ‘low risk’ category, GPs are offered the option of either referring them to a TIA clinic for specialist review within seven days or of managing the patients themselves in the community. If community management is selected, a step-by-step outline is provided with links to pre-populated relevant prescriptions, radiology referral forms, and a variety of patient information leaflets (Figure 3). If patients are triaged into the ‘high risk’ category, GPs are advised to refer them to hospital immediately for specialist assessment and diagnostic work-up to be achieved within 24 hours, and GPs are not offered the community management option. However, if a GP feels that urgent hospital referral is not appropriate in any given situation (*e.g.*, the patient refuses to attend the Emergency Department), then GPs have the option to override this recommendation and refer patients to an outpatient specialist TIA clinic instead, as long as a reason for overriding the recommendation is specified. Hospital referral forms are automatically generated and contain all information needed for specialists to prioritize patients appropriately. In the case of a hyper-acute stroke with unresolved symptoms that started within the preceding 4.5 hours (*i.e.*, within the thrombolysis window) the tool is immediately aborted and the GP is advised to call 111 for emergent hospital transfer to a centre where stroke thrombolysis is available.

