### Outcome measures

The two primary outcome measure are recurrent stroke within 90 days of initial presentation with TIA or stroke and management in accordance with New Zealand TIA guidelines with regard to: treatment with anti-platelet therapy being achieved within 24 hours of presentation; treatment with statin, anti-hypertensive, and/or warfarin (if applicable and not contraindicated) being achieved as soon as clinically indicated and deemed safe; and receipt of appropriate diagnostic investigations within 24 hours or seven days based on risk stratification.

Secondary outcomes include: adverse events (including, but not limited to, medication side effects, diagnostic delays, and misdiagnoses); occurrence of recurrent TIA, myocardial infarction, major bleeding, and/or death within 90 days; implementation of a comprehensive adjuvant treatment plan (smoking cessation counseling, exercise/diet advice, communication of driving restrictions, and education on thrombolysis); overall treatment cost (including both direct cost relating to treatment of index event and cost of any events related to presenting complaint during the follow-up period); and GP and TIA clinic specialist satisfaction.

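### The definition of a significant adverse event leaves out events handled only in the Emergency Department or a clinic, and the undercount may differ between arms

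*Protocol article*

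**What the plan says.** The Background of the protocol article gives the aim as to "formally test the efficacy and safety of New Zealand’s TIA/stroke decision support tool in comparison with usual care". Under Outcome measures the secondary outcomes include "adverse events (including, but not limited to, medication side effects, diagnostic delays, and misdiagnoses"; no type of health-care contact is required.

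Study data lists what is abstracted. One item is "any significant adverse events attributable to medications prescribed after index event, diagnostic delays, and/or misdiagnosis". A significant event "is defined as an event that prompted a GP visit/phone call, hospitalization or death". Emergency Department attendance without admission and TIA-clinic or other outpatient contact are not on that list. In the same list, "TIA, stroke, MI, major bleeding or death within three months of index event" is a separate item with no contact condition.

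The Intervention section describes how the tool directs care. For low-risk patients, "GPs are offered the option of either referring them to a TIA clinic for specialist review within seven days or of managing the patients themselves"; for high-risk patients, "GPs are advised to refer them to hospital immediately for specialist assessment and diagnostic work-up to be achieved within 24 hours". Control practices carry on with routine care.

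**The concern.** The threshold depends on which service was contacted, not on how serious the event was. A side effect that leads to a call to the practice counts. The same side effect treated in the Emergency Department and sent home, or dealt with only at the TIA clinic, does not. These are core settings of this trial: all practices in the chosen districts have access to a TIA clinic, and the clinic is one of the three triage destinations recorded for each patient.

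Two things are at stake. First, the adverse-event outcome is undercounted whenever an event is handled only in an omitted setting. Misdiagnosis and diagnostic delay are the kinds of event that may first come to light at specialist review. Second, the tool is meant to alter the path of care. The Background says that it promotes starting treatment at the first contact instead of waiting for the specialist, and the Intervention section shows it steering patients to hospital, clinic or community care. If side effects tend to return to whoever started the drug, the chance that an event is counted could differ by arm even when the true risk does not. Safety is half of the stated aim, so the comparison of adverse events should not partly reflect the place of care.

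**Working it through.** **Which events the threshold reaches.**

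| Event | Contact condition in Study data? |
|---|---|
| Stroke, TIA, myocardial infarction, major bleeding, death | No; recorded separately |
| Other event attributable to medication, diagnostic delay or misdiagnosis, with GP contact, admission or death | Yes, and it is met |
| The same kind of event, handled only in the Emergency Department without admission, or only in a TIA or outpatient clinic | Yes, and it is not met |

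The gap is the last row. The outcome as worded under Outcome measures would include that row.

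**What the gap could do to the comparison.** The article gives no adverse-event rate and no split of events by setting, so there is no plan figure to reproduce. The inputs below are assumptions.

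- r = true risk of such an event, the same in both arms; 10% assumed.
- s_C and s_T = share of those events handled only in an omitted setting, in the control and tool arms; 10% to 40% assumed.
- Counted risk = r × (1 − s).
- Apparent risk ratio, tool to control = (1 − s_T) / (1 − s_C). The true risk r cancels.

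| s_C | s_T | Counted, control | Counted, tool | Difference (points) | Ratio |
|---|---|---|---|---|---|
| 20% | 20% | 8% | 8% | 0 | 0.80/0.80 = 1.00 |
| 30% | 20% | 7% | 8% | +1 | 0.80/0.70 = 1.14 |
| 40% | 20% | 6% | 8% | +2 | 0.80/0.60 = 1.33 |
| 40% | 10% | 6% | 9% | +3 | 0.90/0.60 = 1.50 |
| 20% | 40% | 8% | 6% | −2 | 0.60/0.80 = 0.75 |

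With equal shares there is no bias in the ratio, only an undercount of s in each arm. With unequal shares the ratio moves in either direction.

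**Scale in this trial.** The planned total of 292 gives 146 per arm. In the third row, 146 × 0.08 = 11.7 events against 146 × 0.06 = 8.8, a gap of about three events. Using the article's intra-class correlation of 0.01 and seven patients per practice, the design effect is 1 + (7 − 1) × 0.01 = 1.06, and the effective size is 146/1.06 = 137.7 per arm. At that size, the chance that a two-sided 5% test calls the artefact significant is about 5% to 16% across the four unequal rows. The likely harm is a distorted estimate, not a false significant result.

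**The case against.** The strongest reply is that the events that matter most are already protected. A reader might infer that any bleed treated and discharged from the Emergency Department goes uncounted. The text does not support that: major bleeding is its own item with no setting condition, so at most a non-major bleed handled solely there is lost. The safety threats named in the Background, missed TIA and needless treatment, can also be examined from the specialist-confirmed final diagnosis, the triage destination and the treatment timings, none of which depends on this definition. This stands and limits the point to the remaining adverse events.

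Second, events seen in the Emergency Department or clinic are not lost as a class. They count if they also led to a GP visit or call, or to admission. Hospitalization is not defined in the article and could be meant to include Emergency Department care; a full protocol or data form may settle that. This also stands. It does not help with clinic-only events, and the list as printed names neither setting.

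Third, a reader might infer that the tool makes the chance of counting an event differ by arm. The Intervention section describes the route of the index presentation only. That later side effects follow the same route is a reasonable inference, but the article does not state it, and control GPs also send patients to hospital, clinic or community care. The shares used above have no source in the article. This objection removes any claim to a known bias; it leaves the possibility of one.

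Finally, widening the definition to events picked up at scheduled reviews could itself bias the count, because the tool may change how many such reviews a patient has. That is right, and the fix allows for it.

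**Conclusion.** The point holds in a limited form. For adverse events attributable to medication, diagnostic delay or misdiagnosis, the Study data definition leaves out those handled solely in the Emergency Department without admission or solely in a TIA or outpatient clinic. It is therefore narrower than the outcome it is meant to supply. Stroke, TIA, myocardial infarction, major bleeding and death are untouched.

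The undercount may differ between arms because the tool steers the setting of care and who starts treatment. The documents give neither its size nor its direction. The range of 0.75 to 1.50 for the apparent ratio rests on the assumed shares and an equal true risk in both arms; with equal shares it is 1.00. It should not be read as evidence that the tool will look safer or less safe than it is. The matter concerns one component of a secondary outcome. It deserves correction because safety is part of the aim and the correction is cheap.

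**What to change.** Redefine a significant event in Study data as one that prompted any unscheduled health-care contact (GP, Emergency Department, outpatient or TIA clinic, ambulance), hospitalization or death. Abstract it in the same way in both arms from the GP and hospital records that are already reviewed. Align this wording with the adverse-event outcome under Outcome measures, so that the outcome and the data collected for it match. Report events found only at scheduled reviews as a separate line, because the number of such reviews may differ by arm.

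The cost is one changed definition on the data form, slightly more abstraction and a somewhat higher event count in both arms. Ambulance and specialist consultations are already collected for the cost comparison in both arms, so part of the information is to hand.

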### Analysis

This is a single-blinded study with the statistician analyzing the results blinded to the study group of participants. The statistician analyzing the data will be based in a different geographical site from the team managing the study and collecting the data. The analyst will be provided with a data file from which all patient, practice, and study group identifying data has been expunged. These variables will be replaced in the analyst’s file with non-identifiable numeric codes. Before being provided with the data file for analysis, the principal investigator and one other investigator will check the data to ensure that all potentially identifying information has been removed.

The analysis will use a generalized linear mixed model to take account of both the dichotomous outcome variables and the cluster design. These models are more complex than generalized linear models or mixed linear models. The outcomes for individual patients will be the response variables, but we will take account of the cluster design and plan to fit practice and practice-treatment interaction effects as random effects. We may have to explore if the practice-treatment interaction effect has a non-zero value and fit a simpler model. PROC GLIMMIX in SAS will be used to fit the models [28-30].

Analysis of the outcomes will include all patients registered by the GPs, including those who eventually turn out to have a diagnosis other than TIA/stroke (*i.e.*, ‘intention-to-treat’ analysis). However, a pre-specified secondary analysis is of the main outcomes for only patients who were confirmed to have suffered an actual TIA or minor stroke by specialist assessment.

### Cost comparisons

This study is focused on short-term costs and consequences of the proposed intervention, occurring within three months of the initial TIA or stroke.

All costs will be measured as at a specified date. For example, as 'dollars in year 2010 prices,’ or 'year ending in June 2011.’ Costs measured in dollars of another date will be adjusted using appropriate price or cost indices to the chosen 'base date.’ The chosen date will be the latest period, at the time of carrying out the analyses, for which the necessary price or cost indices are available. All costs will be measured excluding Goods and Services Tax (GST). This means that any raw data will be clearly identified as either including or excluding GST, and, in the former case, adjusted to remove GST.

The costs associated with using the intervention (purchase of the computer module from BPAC plus any installation, training, and support costs) will be included in the cost analysis. These costs apply of course to the 'intervention arm' only. Other costs will be collected in tandem with the collection of clinical information, for both 'intervention' and 'control' arms of the trial. That is, costs will be collected for every individual reporting to a practice in the trial with a TIA/stroke. The advantage of collecting data at individual level is that standard deviations and confidence intervals for the cost estimates can then be readily calculated [31]. Also, simulation techniques can subsequently be applied, if desired, to assess the robustness of the conclusions reached from the research.

Costs will be collected for the following: GP visit; ambulance/transport cost; specialist consultation; hospital stay; investigations (ECG, CT, carotid ultrasound, MRI, echocardiogram, Holter monitor, laboratory tests); medications (hospital and ex-hospital).

In general the approach to costing will follow that laid down in Pharmac’s latest (2012 edition) *Prescription for Pharmacoeconomic Analysis*[32]. (Pharmac is the New Zealand agency that decides which pharmaceuticals qualify for government subsidy, and the amount of subsidy). Where applicable 'standard costs' given in the *Cost Resource Manual*[33] provided by Pharmac, such as the average cost per GP consultation, will be used. For consultations and medications any subsidy to patients will be added back to give total cost pre-subsidy. For hospital admissions (day-patient or in-patient), the appropriate diagnosis-related grouping cost-weight will be used and length of stay data will also be collected for collateral information.

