In New Zealand, providing 24-hour, seven days a week, rapid access specialist TIA clinics is challenging, especially in the smaller district health boards (DHBs), where patient numbers cannot support a sufficient number of neurologists/stroke physicians to staff an around-the-clock specialist service. A UK study has shown that most patients experiencing TIA or minor stroke first seek healthcare from their general practitioner (GP) [12], even when the event occurs outside normal working hours. Thus, in a setting of limited specialist access it seems logical to look for ways that urgent intervention could be offered at the GP level in order to avoid unnecessary and potentially life-threatening treatment delays. However, the scope of clinical conditions managed in general practice is very broad, and individual GPs will have patients presenting to them with TIA/stroke relatively infrequently. Our analysis of general practice records suggests that, on average, a GP will be consulted four to five times per year by a patient presenting with a presumed TIA/minor stroke. However, GP diagnostic accuracy of TIA/minor stroke is only 50% to 80% [13], so the actual rate of recognized TIA/minor stroke patients encountered by GPs may be as few as two to three patients per year.

Electronic clinical decision support systems (EDS) may be especially valuable for assisting clinical decision-making in such circumstances, where a condition is both challenging to diagnose correctly and encountered by generally clinicians relatively infrequently. New Zealand’s MidCentral Stroke Service, in collaboration with the Best Practice Advocacy Centre Inc. (BPAC), has developed a novel TIA/stroke EDS tool. The tool may mitigate the problem of limited or delayed specialist assessment in a setting in which many GPs lack the experience necessary to manage TIA/stroke independently. It aids GPs to accurately diagnose TIAs, promoting treatment initiation at first point of contact rather than awaiting specialist review, and prompts GPs to manage TIA and stroke patients comprehensively and in accordance with New Zealand guidelines [13].

One of the benefits of the EDS tool is that it is inherently educational, providing GPs with immediate feedback on diagnosis and guideline based advice, which can be applied to the management of future patients and improve diagnostic and management skills over time.

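### The listed costs of the decision support tool omit the GP's time in running it, and an average price per consultation cannot pick that time up, so the tool's cost is probably understated by a small amount

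*Protocol article*

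**What the plan says.** The Cost comparisons section commits to including the costs of using the intervention and spells them out as "purchase of the computer module from BPAC plus any installation, training, and support costs". These apply to the intervention arm only. For every patient in both arms, resource use is collected: "Costs will be collected for the following: GP visit; ambulance/transport cost; specialist consultation; hospital stay", followed by investigations and medications. On unit prices, the section follows a national pharmacoeconomic guide in general. Where applicable it takes standard costs from the accompanying manual, "such as the average cost per GP consultation, will be used". Patient subsidies are added back.

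The Intervention section (text following Figure 1) describes the GP's work with the tool: "Completing the page of background and clinical presentation data takes approximately two to five minutes", depending on familiarity. For low-risk patients the GP may refer to a TIA clinic "or of managing the patients themselves in the community". In the second case, "a step-by-step outline is provided with links to pre-populated relevant prescriptions, radiology referral forms, and a variety of patient information leaflets". The Background gives the aim as "promoting treatment initiation at first point of contact rather than awaiting specialist review".

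Overall treatment cost is a secondary outcome (Outcome measures). The Discussion names the excluded economic items: lost productivity, post-hospital institutional care, nursing and social services, and QALYs. It expects that including the excluded costs would favour an effective intervention. GP time is not mentioned there.

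**The concern.** The protocol names a resource that the intervention uses, the GP's minutes at the data page, and then defines the intervention's cost without it. The only other place where those minutes could be counted is the price of the GP visit. That price is an average per consultation and does not change with length. In the control arm the button click registers the patient and routine care continues, so there is no tool to run.

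The results are meant to help district health boards decide on wider implementation and GPs decide whether to use the tool. GPs are the ones who would give the time. The Discussion's account of what was left out also suggests that the omissions are conservative with respect to the tool. This one probably runs the other way and is not disclosed.

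**Working it through.** The protocol states no cost figure, so there is none to reproduce. The check sets the cost rules against the described workflow and then gives a scale.

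**1. Where GP effort enters the costing**
- Module purchase, installation, training and support: costed, intervention arm.
- Each GP visit, including any additional or follow-up visit: costed, both arms, at a standard average price where applicable.
- Investigations and medications ordered by the GP: costed, both arms.
- Minutes spent running the tool within a counted visit: in no listed item. The average visit price is the same with or without them.
- Minutes spent on community work-up within a counted visit: likewise unpriced, but in both arms. The Study data section records the initial GP triage destination, with community as one option, for patients in the study generally.

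**2. Size per registered patient**

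Input: m = 2 to 5 minutes (Intervention section). Assumption: visit length L, which the documents do not give. Share of one GP visit = m / L.
- L = 10: 2/10 = 20% to 5/10 = 50%.
- L = 15: 2/15 = 13% to 5/15 = 33%.
- L = 20: 2/20 = 10% to 5/20 = 25%.

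These are gross shares. If r minutes of history-taking or form-writing are replaced, the net share is (m − r) / L, which reaches zero when r = m.

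**3. Size over the arm**

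Inputs: 44 practices recruited (Practice engagement); 2.5 full-time-equivalent GPs per practice and 4 to 5 registered patients per GP over 12 months (Sample size calculation). Assumption: an even split, giving 22 practices in the tool arm.
- Uses: 22 × 2.5 × 4 = 220 to 22 × 2.5 × 5 = 275.
- Gross time: 220 × 2 / 60 = 7.3 hours to 275 × 5 / 60 = 22.9 hours.

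**4. Scale against an avoided specialist consultation**

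Assumptions: L = 15 and a specialist visit priced at k = 2 to 8 GP visits (no prices are given). Offset = (m / L) / k.
- Lowest: (2/15) / 8 = 1.7%.
- Highest: (5/15) / 2 = 16.7%.

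**5. Community work-up**

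No time is stated. If it added an assumed 15 to 30 minutes to the same visit at L = 15, the unpriced part would be 15/15 = 1 to 30/15 = 2 GP visits for each patient so managed. This is illustrative and would apply to such patients in either arm.

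**The case against.** The strongest reply is that two to five minutes is the time to complete a form, not the net addition to a visit. The form covers presenting history and a brief focused examination, which a control GP would also be expected to do. Past history is filled in automatically, prescriptions and radiology forms are pre-populated, and hospital referral forms are generated. The net time could be smaller, zero or even negative. This stands: the stated minutes are an upper figure for running the tool, and the direction is likely rather than proven.

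Second, pricing by consultation under a named national guide is an accepted convention. The qualifiers (in general, where applicable) leave room for another GP price, and an article need not list every unit cost. This stands in part. The convention is legitimate and no error in itself, and no alternative price is stated. The article does itemise the tool's cost, and the item is absent from that list.

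A reader might go further and infer that specialist visits avoided are credited in full while the GP work replacing them costs nothing, tilting the comparison towards the tool. The documents do not support that:
- Extra GP visits, investigations and medications are costed in both arms.
- Control GPs may also manage patients in the community.
- Community management is only an option, and only for low-risk patients in the tool arm. Nothing says specialist visits will fall overall.
- The excluded post-hospital costs would work in the tool's favour if included and if the tool is effective.

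Nor can the omitted time be compared with the module's cost, since no module price is given.

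**Conclusion.** The point holds in a limited form. GP time per use of the tool is absent from the listed intervention costs, and an average price per consultation cannot recover it. The tool's cost is therefore probably understated, by at most the two to five gross minutes per registered patient for running the tool. That is 13% to 33% of a GP visit at an assumed 15 minutes, and 10% to 50% over assumed lengths of 20 down to 10 minutes. Under an even split of practices and the protocol's planning averages, it comes to roughly 7 to 23 GP hours over the arm.

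In-visit time for community work-up is also unpriced, but its length is not given and it is not confined to one arm. The net effect on the cost difference between arms is not established. Only a secondary outcome is affected; the two primary outcomes are not. This is an inexpensive improvement rather than a flaw that threatens the trial.

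**What to change.** - Add a GP-time component for tool use to the intervention costs in the Cost comparisons section. Vary it over 0 to 5 minutes per use, or take it from BPAC system logs if these record it. Price it per minute from the same standard cost source as the GP consultation, and state the visit length used to convert a price per visit to a price per minute.
- Add a sensitivity analysis that prices visits with GP community work-up as extended rather than average consultations. Apply it in both arms, using the recorded initial triage destination.

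The cost is one more line in the costing and one sensitivity analysis, with no new patient data. The cost result may become slightly less favourable to the tool.
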